#### 5.4.7.1 Concomitant Medication and Lifestyle Management

From screening until the 24-month follow-up, all antidiabetic medications (OADs and insulin, including dose adjustments, interruptions, or discontinuations) as well as concomitant medications required by the protocol must be recorded in the electronic case report form (eCRF).

Treating physicians may adjust antidiabetic therapy or prescribe other concomitant medications according to standard clinical practice. Subjects will also receive counseling and guidance on lifestyle management for diabetes.

#### 5.4.7.2 Concomitant Antidiabetic Therapy and Lifestyle Management

Subjects must be on stable OAD therapy for at least 3 months prior to the baseline procedure (subjects taking α-glucosidase inhibitors must undergo a 2-week washout before enrollment). After EDN, OADs and insulin regimens will be adjusted by the investigator according to blood glucose levels and guideline recommendations (see Sections 5.4.7.3 and 5.4.7.4). All changes in OADs and insulin type/dose must be documented at follow-up visits.

#### 5.4.7.3 Principles for Rescue Treatment of Hyperglycemia

For subjects meeting any of the following hyperglycemia definitions, and where no definite cause can be identified, investigators may initiate insulin therapy on top of existing treatment as rescue therapy, based on clinical judgment.

**Study Period Criteria (≥2 weeks of 4-point SMBG daily mean):**

- 4 weeks post-EDN: FBG ≥ 13.9 mmol/L
- 8 weeks post-EDN: FBG ≥ 11.1 mmol/L
- 8 weeks post-EDN: HbA1c ≥ 8.5%

**Recommended principles of rescue treatment for hyperglycemia:**

- Initiate insulin therapy in addition to existing treatment, including intensifying basal insulin dose and/or adding short-acting or rapid-acting insulin.
- Adjust basal insulin dose every 3–5 days according to fasting blood glucose (FBG). Increase by 1–4 U per adjustment until target FBG is achieved. The maximum basal insulin dose should not exceed 0.5–0.6 U/kg/day.

#### 5.4.7.4 Principles for Medication Adjustment in Hypoglycemia

Hypoglycemia is an adverse event requiring special attention after EDN. Hypoglycemia is defined as blood glucose <3.9 mmol/L.

**Management principles:**

- If hypoglycemia occurs, immediately administer 15–20 g glucose and recheck blood glucose after 15 minutes.
- In subjects receiving insulin therapy, glycemic targets should be relaxed to strictly avoid recurrent hypoglycemia for several weeks, to partially reverse hypoglycemia unawareness and reduce future risk.
- Medication reduction should follow the sequence: Insulin (if applicable) → Sulfonylureas → Glinides → Thiazolidinediones → Metformin (final adjustment of metformin at investigator’s discretion).

#### 5.4.7.5 Principles of Lifestyle Management

During the study, qualified healthcare professionals will provide diabetes management counseling at each visit, including dietary and exercise guidance, and education on the signs, symptoms, and treatment of hypoglycemia (if it occurs).

**Lifestyle management principles:**

- Subjects should continue their usual physical activity and follow a healthy diet plan (consistent quantity and timing of meals) throughout the study.
- Dietary counseling may be reviewed as needed during the study.
- Apart from lifestyle measures required for diabetes care, subjects should not initiate structured diet and/or exercise weight-loss programs during the study.

#### 5.4.7.6 Periprocedural Medication Requirements

**Analgesia/Sedation for EDN Procedure**

In addition to local anesthesia at the puncture site, appropriate analgesic and sedative medications should be administered during EDN according to local standards to reduce pain/discomfort, maintain hemodynamic stability, and ensure procedural tolerability and efficacy. Oxygen supplementation via mask or nasal cannula is recommended. Morphine sulfate or fentanyl combined with midazolam may be used (dosages determined by investigators per standard care and patient condition). Additional doses may be administered during ablation if necessary.

**Antiplatelet Therapy**

To minimize thrombotic complications, antiplatelet therapy (monotherapy) should be initiated before the procedure, such as aspirin (ASA) or a P2Y12 inhibitor (clopidogrel preferred; ticlopidine may be used if intolerant). Subjects already receiving ≥72 hours of ASA or a P2Y12 inhibitor do not require a loading dose.

Otherwise, a loading dose must be given before or no later than 2 hours after the baseline procedure.

**Recommended minimum loading doses:** ASA 300 mg, clopidogrel 300 mg.

**Anticoagulation**

Standard intraoperative heparinization should be administered, or other anticoagulation selected as clinically appropriate. Intraoperative activated clotting time (ACT) should be maintained at ~250 seconds.

Post-procedure antiplatelet therapy should be continued for at least 1 week post-procedure. Minimum daily maintenance doses: ASA 75 mg/day or clopidogrel 75 mg/day.

Note: To reduce bleeding risk, subjects on long-term anticoagulation should not receive additional antiplatelet therapy.

### 5.4.8 Enrollment and Baseline Procedure

Subjects meeting all inclusion criteria and no clinical exclusion criteria must complete the following before enrollment:

- Angiography of the abdominal aorta and its branches, with documentation of findings.
- Assessment of angiographic exclusion criteria.

Enrollment is confirmed only when no angiographic exclusion criteria are met. The enrollment time point is defined as insertion of the EDN catheter into the subject.

The baseline procedure starts with insertion of the guiding catheter and ends with its removal after final angiography.

The following intraoperative data must be collected and recorded in the eCRF:

- Procedure date and time (start = guiding catheter insertion; end = removal after final angiography).
- Device information: generator model/serial number, catheter model/batch/serial number (see Table 5-3).

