| **Statistical Methods** | **Sample size estimation:**  No formal sample size calculation was performed. However, the sample size of 30 (treated) was determined based on the hypothesis that patients would experience a reduction in HbA1c at 6 months. To achieve a predefined 1.0% reduction in HbA1c, with a standard deviation of 1.5%, a sample size of 26 would be required to yield a lower two-sided 95% confidence bound of approximately 0. Taking into account a 10% drop out rate, the estimated sample size is 29.  **Populations for analysis:**  Baseline characteristics were analyzed in all enrolled patients. The treated patients were analyzed for safety profile, and patients with follow-ups were analyzed for efficacy.  **Analysis of primary endpoints:**  All adverse events were recorded by and assessed by all investigators for the association with the device or procedure. HbA1c reductions at 6 months were measured for patients with 6-month follow-up and expressed as mean with a 2-sided 95% CI.  The success criterion for this study is defined as no device- or procedure-related MAE occured and achievement of HbA1c reduction at 6 months. |

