# Study Design

## 5.1 Overall Design and Rationale

The feasibility clinical trial of endovascular denervation for the treatment of T2DM is a prospective, multicenter, single-arm feasibility study. The study will employ the EDN system (including generator and catheter) developed by Shanghai Brattea Medical Technology Co., Ltd. to perform EDN in the celiac trunk and hepatic artery for T2DM treatment.

As this is an early feasibility study of EDN for T2DM, and no device with the same indication has yet been approved for registration in China, a single-arm design was selected. Additionally, the primary study endpoints are not significantly influenced by placebo effects or psychological factors, making this design appropriate.

During EDN, anticoagulation will be administered according to clinical standards. Antiplatelet therapy will be used pre- and post-procedure to prevent thrombosis. Dynamic safety monitoring will be conducted throughout the trial to minimize patient risk. All enrolled subjects who undergo EDN will be followed for 24 months post-procedure.

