### 5.2.3 Subject Withdrawal Criteria and Procedures

#### **5.2.3.1 Enrollment Time Point**

A subject is considered eligible for the study after signing an informed consent form approved by the ethics committee, meeting all inclusion criteria, and not meeting any exclusion criteria. The official enrollment time point is defined as the moment the EDN catheter is introduced into the subject’s body.

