## 5.3 Evaluation Methods

### 5.3.1 Primary Endpoints

#### **5.3.1.1 Primary Safety Endpoint**

The primary safety endpoint is the incidence of composite major adverse events (MAE)* related to the investigational device and/or ablation procedure occurring intraoperatively or within 30 days post-baseline procedure.

- MAE is defined to include the following events:
- Hypoglycemia or hyperglycemia requiring hospitalization.
- Vascular complications requiring surgical repair, interventional treatment, thrombin injection, or blood transfusion.
- Celiac/hepatic artery dissection or perforation requiring intervention.
- Significant embolic events leading to end-organ damage or requiring intervention to prevent end-organ damage.
- Acute liver injury or liver failure.
- All-cause mortality.

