#### 5.5.2.2 Pre**-**EDN Angiography

① Identify a puncture site ~1 cm inferior to the midpoint of the right groin; infiltrate with 2% lidocaine for local anesthesia.

② Perform right femoral arterial access using the Seldinger technique and place an 8F vascular sheath.

③ Advance a 5F pigtail catheter over a 0.035-inch hydrophilic (loach-type) guidewire through the sheath; position the catheter tip at the superior margin of T12 and perform abdominal aortography (DSA) to delineate the morphology and course of the celiac axis and branches, and to confirm whether angiographic exclusion criteria are present.

④ If no angiographic exclusion criteria are met, the subject may be enrolled in this clinical study.

⑤ Remove the pigtail catheter. Using a coaxial technique, advance a 5F hepatic artery catheter (Rh catheter) and an 8F guiding catheter over a 0.035-inch guidewire. Position the tip of the guiding catheter in the proper hepatic artery.

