## 6.4 Statistical Methods

**Statistical Analysis Sets**

Primary, secondary, and additional endpoints will be analyzed using both the Intent-to-Treat (ITT) and Per-Protocol (PPS) populations.

ITT: All subjects who signed written ICF and were enrolled, regardless of whether EDN was successfully performed.

PPS: Subjects who underwent EDN in the celiac/hepatic arteries using the investigational device.

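### Subjects who have arterial access or a guiding catheter placed but never receive the EDN catheter are in no analysis set, so a complication that aborts the case is left out of the primary MAE rate

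*Protocol*

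**What the plan says.** **Enrolment.** Section 5.4.8: "The enrollment time point is defined as insertion of the EDN catheter into the subject". Section 5.2.3.1 agrees: "The official enrollment time point is defined as the moment the EDN catheter is introduced into" the subject's body. Section 5.4.3 sets it at entry of the EDN catheter into the guiding sheath, and the Protocol Synopsis at catheter insertion.

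**What comes first.** Section 5.5.2.2 lists femoral access with an 8F sheath, aortography, the angiographic exclusion check, and then an 8F guiding catheter: "Position the tip of the guiding catheter in the proper hepatic artery". Only in section 5.5.2.3 is the EDN catheter advanced through that guiding catheter.

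**Procedure and endpoint window.** Section 5.4.8: "The baseline procedure starts with insertion of the guiding catheter and ends with its removal after final angiography". Section 5.3.1.1 counts related MAEs "occurring intraoperatively or within 30 days post-baseline procedure".

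**Analysis sets.** Section 6.4 defines ITT as "All subjects who signed written ICF and were enrolled, regardless of whether EDN was successfully performed", and restricts PPS to subjects who underwent EDN. The Data Analysis paragraph of 6.4 summarises safety endpoints in all enrolled subjects. The front synopsis (Clinical Study Protocol Synopsis) differs: "The treated patients were analyzed for safety profile, and patients with follow-ups were analyzed for efficacy".

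**Follow-up.** Section 5.1: "All enrolled subjects who undergo EDN will be followed for 24 months post-procedure". Section 5.4.9 requires Day-7 or discharge tests for enrolled subjects.

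**Success criterion.** The front synopsis requires that no device- or procedure-related MAE occurred, together with an HbA1c reduction at 6 months.

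**The concern.** The procedure, as the protocol defines it, begins before the population in which its safety is measured exists. Someone who is punctured and catheterised for the trial but stopped before the EDN catheter goes in contributes to neither numerator nor denominator.

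This exclusion is informative. A hepatic or celiac dissection caused by the guiding catheter, or a bleed at the access site, is itself a reason to stop. Both can be MAEs under section 5.3.1.1, which includes dissection or perforation needing intervention and vascular complications needing repair, thrombin injection or transfusion. Section 9.1 lists access-site complications, dissection and perforation among the expected procedural risks. The front synopsis also allows screen failures to be replaced, so an aborted case could be replaced without a trace in the endpoint.

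The criterion tolerates no related MAE. Dropping these subjects can only help it to be met.

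**Working it through.** The point rests on definitions; the protocol states no figure for it that could be reproduced. The first step is to follow a subject through the sequence and see where each stopping point falls.

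| Last step reached | Inside the baseline procedure as defined in 5.4.8 | ITT (6.4) | PPS (6.4) | Treated set (front synopsis) |
|---|---|---|---|---|
| Sheath and aortography | No (but 5.4.3 places angiography during the procedure) | No | No | No |
| Guiding catheter in place, no EDN catheter | Yes | No | No | No |
| EDN catheter in, no ablation | Yes | Yes | No | No |
| Ablation delivered | Yes | Yes | Yes | Yes |

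The second row is the clear contradiction: inside the procedure, outside every set. The first row is a gap whose size depends on when the intraoperative period is taken to begin. The third row is a conflict between section 6.4 and the front synopsis.

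**Effect of one case.** Inputs: 30 subjects treated (front synopsis); one further subject, assumed, with an MAE before EDN-catheter insertion that stops the case and is judged procedure-related; no other MAE. Exact Clopper-Pearson 95% limits:

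1. Present sets, 0/30: rate 0%. Upper limit = 1 − 0.025^(1/30) = 0.1157, so 0 to 11.6%. No MAE is counted, and the safety part of the criterion is met.
2. Set starting at arterial puncture, 1/31: rate = 1/31 = 3.2%. Lower limit = 1 − 0.975^(1/31) = 0.0008. The upper limit solves (1 − p)^31 + 31p(1 − p)^30 = 0.025, giving p = 0.1670. So 0.1 to 16.7%. One MAE is counted, and the criterion is not met.

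**How likely a missed MAE is.** The documents give neither a pre-insertion MAE risk nor an abort rate. Let p be the risk per subject of a pre-insertion MAE and q the share of such MAEs that stop the case. With 31 subjects accessed, P(at least one missed) = 1 − (1 − pq)^31.

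- Assumed p = 0.01: from 0 at q = 0 to 1 − 0.99^31 = 27% at q = 1.
- Assumed p = 0.02: from 0 at q = 0 to 1 − 0.98^31 = 47% at q = 1.

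The 27% and 47% are upper bounds for those assumed risks, because they need every pre-insertion MAE to abort the case.

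**Direction of bias.** For the zero-MAE criterion, the exclusion can only hide events. For the rate, it biases downward when MAEs are more frequent among stopped subjects than among enrolled ones. That is the expected direction, since a complication is a cause of stopping. Uncomplicated angiographic exclusions pull the other way, by adding to the denominator once included.

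**The case against.** Several points on the other side are sound.

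- **Most such events are still counted.** A reader might infer that all MAEs from access and guiding-catheter steps are missing from the endpoint. The text does not support that. The endpoint covers the intraoperative period, the baseline procedure starts at the guiding catheter, and AE assessment is among the intraoperative data in 5.4.8. Nothing removes an early event in a subject who later receives the EDN catheter. This stands and limits the point to subjects who never reach that step.
- **Sheath and aortography precede the defined start.** Under 5.4.8 an access bleed before the guiding catheter may not be intraoperative. This stands as an ambiguity, because 5.4.3 places baseline angiography during the procedure.
- **Attribution may exclude these events anyway.** Sections 5.3.1.1 and 6.1 require a relation to the device and/or the ablation procedure; the front synopsis speaks of the procedure generally. With no device used and no ablation, the narrower wording might not be met. This stands, and the 1/31 figure assumes the broader reading.
- **Enrolment might be read earlier.** Section 5.5.2.2 says the subject may be enrolled once angiography is clear, before the guiding catheter. But 5.2.3.1, 5.4.3 and 5.4.8 each fix the moment explicitly at the EDN catheter, so this only adds an inconsistency of order.
- **The events may still be reported.** The AE definition covers study-required procedures, and the hospitalisation note under Table 12-1 requires reporting of complications after consent. Section 12.2, however, runs from consent and enrolment together, which is unclear for someone never enrolled. What is shown is loss from the analysis sets, not from all safety reporting.
- **This is a feasibility trial without a formal hypothesis.** True, and it lowers the severity. The front synopsis nevertheless sets a success criterion that one event defeats.

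**Conclusion.** The concern holds for subjects with arterial access or a guiding catheter but no EDN catheter. They are in no analysis set and have no scheduled 30-day visit, although for those with a guiding catheter the protocol's own baseline procedure has begun. One such case with an MAE judged procedure-related moves the result from 0/30 (0 to 11.6%) to 1/31 = 3.2% (0.1 to 16.7%) and reverses the safety part of the success criterion. This assumes the broad attribution wording and no other MAE.

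Three stronger readings are not supported. The 27% and 47% are not estimates of the chance of a missed MAE. The front synopsis does not settle that enrolled but unablated subjects are dropped, because section 6.4 keeps them in ITT and in the safety summary; the two texts conflict. And the unexplained 37 patients in the front synopsis, against about 30 treated, cannot be read as seven aborted cases.

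This should be fixed. It is not a must-fix, since the trial is a feasibility study and the documents do not show how often the gap would arise.

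**What to change.** 1. **Safety set (6.4 and front synopsis).** Define one safety set: all consented subjects in whom arterial puncture for the study procedure was started, whether or not the EDN catheter was inserted or ablation delivered. This also resolves the conflict between treated and all enrolled subjects. Report the treated-only rate as supportive.
2. **Window and attribution (5.3.1.1 and 6.1).** Start the intraoperative window at arterial puncture. Use one attribution wording throughout, including both synopses, under which access and guiding-catheter events count.
3. **Data collection (12.2, 5.1, 5.4.9 and 5.4.10).** State that AEs are recorded for accessed but untreated subjects, and add a Day-30 safety contact for them.
4. **Enrolment count.** Leave the 30 subjects tied to EDN-catheter insertion, and align the order in 5.5.2.2 with it.

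The cost is protocol wording, a few extra contacts, and an MAE rate that may look less favourable.

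Separately, and of minor weight, 5.4.8 ends the procedure with guiding-catheter removal after the final angiogram, whereas 5.5.2.3 step 9 removes that catheter before it. The two passages need to be reconciled.

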**Table 5-3 Device performance evaluation**

| **Generator Evaluation** | |
| --- | --- |
| Mode | GL-06E |
| Generator appearance intact and in good condition | □ Good □ Not good |
| Generator can be switched on/off normally | □ Yes □ No |
| Generator can perform self-check at startup | □ Yes □ No |
| Generator allows normal parameter setting | □ Yes □ No |
| Generator can detect surface electrodes | □ Yes □ No |
| Generator can recognize ablation catheter | □ Yes □ No |
| Generator can perform RF ablation normally | □ Yes □ No |
| Surgical interface can display ablation data in real time | □ Yes □ No |
| Ablation data can be stored normally | □ Yes □ No |
| Generator can terminate RF ablation normally after countdown | □ Yes □ No |
| **Catheter Evaluation** | |
| Catheter package intact | □ Intact □ Damaged |
| Catheter appearance normal | □ Yes □ No |
| Catheter basket expansion/retraction performance normal | □ Yes □ No |
| Catheter can smoothly pass through the sheath | □ Yes □ No |
| Catheter pushability in vessel | □ Good □ Fair □ Poor |
| Catheter flexibility | □ Appropriate □ Slightly soft □ Slightly stiff □ Too soft □ Too stiff |
| Electrode visibility under X-ray | □ Good □ Fair □ Poor |
| Catheter positioning controllability | □ Good □ Fair □ Poor |
| Connection cable matches relevant equipment | □ Yes □ No |
| Catheter can perform RF ablation normally | □ Yes □ No |
| Catheter integrity after withdrawal | □ Complete □ Incomplete (please describe): ______ |

- Vessels treated, ablation sites, number of ablation points, ablation duration, and parameters (temperature, power, impedance).
- Other devices or adjunctive therapies used intraoperatively.
- Intraoperative and postoperative medications, including analgesics/sedatives, antidiabetics/insulin, anticoagulants, antiplatelets, and ACT.
- Adverse event (AE) assessment and management, including AE, SAE, SADE, UADE, USADE, and ADE.
- Reconfirmation of inclusion/exclusion criteria.

Note: Metformin must be withheld on the day of DSA.

### 5.4.9 Post-op Day 7 or Before Discharge

All enrolled subjects must undergo CBC and renal/liver function testing at Day 7 post-procedure or before discharge (whichever comes first). Concomitant use of antidiabetics, insulin, and anticoagulants/antiplatelets must be documented. AE/ADE/SAE/SADE and device deficiencies must also be assessed and recorded.

### 5.4.10 30-Day Follow-up (±7 days)

At 30 days post-procedure, subjects must return for follow-up including:

- Physical exam (height, weight, waist & hip circumference, office BP).
- Antidiabetic medication/insulin use.
- Other treatments (cardiovascular, anticoagulant, antiplatelet therapies).
- Laboratory tests: CBC, renal function (BUN, creatinine, eGFR), fasting glucose & insulin, 14-day CGM, HbA1c, HOMA-IR & HOMA-β, lipid profile, liver function (ALT, AST, ALP, TBil, GGT), plasma catecholamines.
- HRV: 24-hour Holter monitoring.
- AE assessment and management (AE, SAE, SADE, UADE, USADE, ADE).

### 5.4.11 3-Month Follow-up (±14 days)

At 3 months post-procedure, subjects must return for follow-up including:

- Physical exam (height, weight, waist & hip circumference, office BP).
- Antidiabetic medication/insulin use.
- Other treatments (cardiovascular, anticoagulant, antiplatelet therapies).
- Laboratory tests: CBC, renal function (BUN, creatinine, eGFR), fasting glucose & insulin, 14-day CGM, HbA1c, HOMA-IR & HOMA-β, lipid profile, liver function (ALT, AST, ALP, TBil, GGT), plasma catecholamines.
- HRV: 24-hour Holter monitoring.
- AE assessment and management (AE, SAE, SADE, UADE, USADE, ADE).

